### **13.0 STUDY LIMITATIONS AND MEASURES TO MINIMIZE IT**

- i) Measurement bias can occur while taking recording or taking measurements (i.e.; recording the weight, height, Blood Pressure, waist circumference). The inter-observer variation can be avoided by training of the staffs conducting the measurements and using same type of instruments. The machines or instruments must be calibrated before use.
- ii) Information bias on physical activity and dietary intake recall. This can occur whereby the respondents might not give the true or exact answers to the questions, either they have forgotten or refused to reveal some information to others. Sometimes, the interpretation of questions might be differently interpreted by the respondents. The limitation unfortunately has to be acknowledged.
- iii) Drop out of participants from the study can occur at any time and without reasons. Therefore, measures have to be taken by conducting regular meeting with the partner organizations to discuss about progress and problems encountered. Immediate action should be taken if any

problems arise. The peer-educator formed among the MDA members can help to track the defaulter cases by means of social visit and follow up.

#### **14.0 ETHICAL CONSIDERATION**

A written consent will be obtained from the patient before any intervention or procedure to be conducted on them. The patient will be informed and explained about the purpose of the study. The patient has the right to refuse or disagree to participate in the study. Participants' safety is the prime concern in this study. The risk to participants in this study is modest primarily when related to physical activity. Adoption of vigorous physical activity regimen can increase the risk of cardiovascular events in previously sedentary individuals; hence this study will focus on adoption of light to moderate physical activity program such as brisk walking and aerobic exercises. The participants will be screened for physical capacity using Physical Activity Readiness Questionnaire (PAR-Q) and will be referred to relevant specialist if required. Participants will be educated about the sign and symptoms of angina and heart attack that they should inform immediately. All potential adverse events of intervention specific to physical exercise, injuries and orthopedic conditions will be recorded, monitored and reported to the Medical Ethics Committee. Ethics clearance will be obtained from the Medical Ethics Committee of UMMC.

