## **6.2 Phase 2:**

### **i) Implementation phase**

This phase will include the various stages as mentioned earlier such as; i) recruitment of high risk adults, ii) screening of high risk adults for eligibility, iii) allocation of participants to either intervention group and usual care group and v) implementation of intervention to both the groups. The community-based healthy lifestyle intervention program (Co-HELP) was designed following review of current evidences [6-7, 24, 43-48] and guidelines [40, 49-50]. The group-based programs was adopted from publicly available materials from the US Group Lifestyle Balance of Diabetes Prevention Program (DPP Research Group) [51], combined with materials from Integrated Educational Module for Non-Communicable Diseases from Ministry of Health Malaysia[52]. Modification was tailored to the needs of the community and cultural sensitivity. Few consultations were done with stakeholders (i.e. dietitian, physical trainers, family medicine specialist, local

community organizations and potential participants) prior to interventions. The education materials were refined and pre-tested on the community-volunteers prior to delivery. The content focus was based on the Health Belief Model approach as its theoretical framework[53]. The 12-month intervention program consisted of two parts comprising of a 6-month active period and a 6-month maintenance period. In total, participants in the intervention group received twelve group-based sessions and minimum of two individual counseling with the dietitian to reinforce behavioural change. Most of the group sessions were held during weekends, at convenient community settings like community hall and recreational park. The first 6-month active period consisted of structured 90 minutes group sessions; biweekly in the first 3 months (Sessions 1-6) and monthly in the next 3 months (Sessions 7-9). During the maintenance period the group sessions were held monthly for three months (Session 10-12) and for the last three months participants were followed up through telephone calls or home visits. All intervention sessions were conducted either in groups of 20 people or smaller groups of 5 – 8 people depending on the type of activities (i.e. lecture, seminar, group work or discussion). Table 1 provides detailed information on session titles, frequency, content focus and the Health Belief Model constructs.

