## **ii) Intervention group**

The lifestyle modification intervention sessions will be conducted in group format, coordinate and facilitate by the community volunteers. The intervention will focuses on empowerment of participants to change their lifestyle. This intervention will incorporates diet, physical activity and healthy behaviour modification. The contact schedule occurs in three phases, with an early 3- month intensive phase ( 1 group session every 2 weeks) followed by a 6-month non-intensive phase ( 1 group session every month) and a 3-month maintenance phase. The goals set for

this intervention is based on what is outlined in the Clinical Practice Guidelines by Ministry of Health Malaysia, Management of type 2 Diabetes Mellitus, 4th edition 2009[40], to produce modest but yet achievable outcomes; reduction of 5-10% of initial body weight for all overweight and obese participants, reduction of calorie intake (20-25 kcal/kg body weight) and increase light to moderate physical activity to at least 150 minutes/ week. The group will have series of different sessions with professionals like Physicians, Dietician/ Nutritionist and Physical trainer specialist during the intensive phase. Throughout the intervention, the participants will have a continuous support from community volunteers that act as program facilitators. Facilitators will consult the professional health providers if any problems arise during the intervention sessions. Participants will also be referred to relevant health providers if the problem could not be handled by the program facilitators.

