#### **6.4 Outcome measures**

The primary outcome measures for this study are fasting blood glucose, 2-hour plasma glucose and HbA1C. Secondary outcome measures are weight, BMI, waist circumference, Total cholesterol, Triglyceride, LDL cholesterol, HDL cholesterol, Systolic and Diastolic blood pressure, physical activity, diet intake and HRQOL. All these will be taken at baseline, six months and twelve months except for HRQOL that will be measured at baseline and twelve months. The primary assessment time-point of this study is at 6-month to measure the immediate effect of the intervention. The final visit which occurred at 12-month will be used to measure sustainability of the intervention.

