## 10.0 DATA COLLECTION

The data collection for both groups will be done at the same interval:

- i) 1st data collection : At baseline
- ii) 2nd data collection: After 6 months
- iii) 3rd data collection: After 12 months

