**Table 8: Summary of data collection and time interval**

| Measurements  | Screening | Baseline | 6-month | 12-month |
|----------------------|------------------|-----------------|----------------|-----------------|
| Questionnaire |                  |                 |                |                 |
| Socio-demography     | X                |                 |                |                 |
| PAR-Q                | X                |                 |                |                 |
| IPAQ-Short form      |                  | X               | X              | X               |
| 24-hour diet recall  |                  | X               | X              | X               |
| SF-36 HRQOL          |                  | X               |                | X               |
| Anthropometry |                  |                 |                |                 |
| Weight               | X                | X               | X              | X               |
| Height               | X                | X               | X              | X               |
| BMI                  | X                | X               | X              | X               |
| Waist circumference  | X                | X               | X              | X               |
| Clinical      |                  |                 |                |                 |
| Blood Pressure       | X                | X               | X              | X               |
| Biochem       |                  |                 |                |                 |
| RBS                  | X                |                 |                |                 |
| FPG                  |                  | X               | X              | X               |
| 2-hPG                |                  | X               | X              | X               |
| HbA1C                |                  | X               | X              | X               |
| Total cholesterol    |                  | X               | X              | X               |
| HDL cholesterol      |                  | X               | X              | X               |
| Triglycerides        |                  | X               | X              | X               |

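### The only adverse-event rule is narrow and ambiguous, has no collection point at the visits common to both arms, and does not say that cardiovascular or diet-related events are recorded

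*Protocol*

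**What the plan says.** Section 14.0 sets the recording rule: "All potential adverse events of intervention specific to physical exercise, injuries and orthopedic conditions will be recorded". These events are then monitored and reported to the ethics committee. No other sentence in the protocol says which adverse events are to be recorded.

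The same section names a cardiovascular risk, "Adoption of vigorous physical activity regimen can increase the risk of cardiovascular events in previously sedentary individuals", and gives a reporting route for it: "Participants will be educated about the sign and symptoms of angina and heart attack that they should inform immediately". It does not say that such reports are entered in the study record.

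On timing, section 10.0 states "The data collection for both groups will be done at the same interval": baseline, 6 months and 12 months. Table 8, titled "Summary of data collection and time interval", lists questionnaires, anthropometry, blood pressure and laboratory tests. It has no adverse-event row at any visit. Section 6.4 lists no safety outcome ("The primary outcome measures for this study are fasting blood glucose, 2-hour plasma glucose and HbA1C", followed by a list of secondary outcomes), and section 12.0 describes no safety analysis.

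Within the programme, section 6.2 ii) gives an escalation route: "Facilitators will consult the professional health providers if any problems arise during the intervention sessions". That section also makes diet one of the components of the programme.

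**The concern.** The rule decides what is recorded by suspected cause and by type of event. Attribution is usually least certain when an event is reported, so a filter at that point removes data that cannot be recovered at analysis. Two gaps follow from the text. A cardiovascular event that nobody links to exercise is not clearly recordable. A suspected diet-related event is not covered, although the programme sets a calorie target and includes individual dietitian plans.

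The second problem is opportunity. With no event question at the visits common to both arms, events will come to light mainly through contact with the study, and that contact is much heavier in Co-HELP. If the results are used to support wider roll-out, as the abstract foresees, a reader will want to know about harms. What would be available is an incomplete list gathered with unequal intensity.

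**Working it through.** The protocol gives no adverse-event rate and no safety power, so there is no figure of its own to reproduce. The check compares the text, counts contacts, and adds an illustration on assumed rates.

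**1. What the rule covers.** The sentence can be read in two ways.
- Narrow: exercise-specific events, injuries and orthopaedic conditions, all of them arising from the intervention.
- Broad: a list of three items, namely events specific to exercise, injuries, and orthopaedic conditions.

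On both readings a cardiovascular event qualifies only through a possible link to exercise, and a diet-related event that is neither an injury nor an orthopaedic condition does not qualify.

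**2. Whether usual care is covered.** The rule speaks of events of the intervention. Section 6.2 i) uses that word for both arms ("implementation of intervention to both the groups"), and section 4.0 and the title of Table 6 also call usual care an intervention. So the arm is not excluded, but no sentence says how or when its events are collected. Table 6 gives both arms the same goals of 150 minutes of activity per week and 5-10% weight loss, so events in usual care are relevant for comparison.

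**3. Scheduled contacts.**
- Co-HELP: 12 group sessions (Table 4) + at least 2 dietitian contacts (section 6.2 i) = at least 14. Phone, e-mail or home follow-up in months 10-12 comes on top, with its frequency not stated.
- Usual care: follow-up depends on the primary care clinic (Table 6), with no number given.
- Both arms: study visits at 6 and 12 months, without an event question.

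The difference in scheduled study contact is therefore at least 14.

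**4. What unequal capture could do (assumed figures).** Assume a true event rate of 10% in each arm of 122 (section 5.8: 244 in total) and full capture in Co-HELP. Expected recorded events are 122 × 0.10 = 12.2 in Co-HELP and 12.2 × c in usual care, where c is the share captured there. The chance of a significant result uses the usual two-proportion formula, two-sided 5%:

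Φ{(d − 1.96·SE₀)/SE₁}, with SE₀ = √[2p̄(1 − p̄)/n] and SE₁ = √[p₁(1 − p₁)/n + p₂(1 − p₂)/n].

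| c | Recorded, Co-HELP vs usual care | Chance of a spurious significant difference |
|---|---|---|
| 75% | 12.2 vs 9.2 | about 10% |
| 50% | 12.2 vs 6.1 | about 32% |
| 25% | 12.2 vs 3.1 | about 68% |

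The capture shares and the 10% rate are not in the protocol. The table shows direction and range and is not an estimate.

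**5. What the trial could detect with complete capture.** By the same formula with n = 122 per arm, 80% power requires, for example, 2% against about 10.8% (power 0.80) or 5% against about 16% (power 0.80). If no event occurred in one arm, the one-sided 95% upper bound would be 1 − 0.05^(1/122) = 2.4%. Steps 4 and 5 treat participants as independent. With one community per arm, any variation between communities would make a real comparison weaker still.

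**The case against.** The protocol can be defended on several points.

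- A reader might infer that usual-care events are lost. The text does not support that. It calls usual care an intervention in several places and never excludes that arm from recording. What stands is that collection there is unspecified.
- A reader might infer that no safety comparison is possible. That is too strong. None is promised in the objectives, outcomes or analysis section, so no stated aim fails, and one could be attempted at the common visits. What stands is that it would be open to ascertainment bias and would have little power.
- A reader might infer that lay facilitators decide causality. No section assigns that judgement to them. Table 4 has professionals delivering the first six sessions and supervising the next six, and facilitators escalate problems.
- Cardiac symptoms do have a reporting route, open to participants without limit to one arm. PAR-Q screening and the exclusion of cardiovascular disease within the past 6 months also address the risk. The remaining gap is that recording of the reports is not stated.
- The rule speaks of potential events, so a possible link is enough, and event recording can be continuous, so a missing row in a summary table does not contradict it. That is fair. A possible link must still be suspected by someone, and continuous recording depends on contact, which is unequal.
- Usual-care participants also see their clinics. They do, but no route from the clinic to the study record is described.

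**Conclusion.** The concern holds as a defect in the recording rule and the visit schedule. The rule is ambiguous and filtered on attribution. It leaves out diet-related events, does not state that cardiovascular events are recorded, and has no scheduled collection in either arm. With at least 14 more scheduled contacts in Co-HELP, an unbiased between-arm statement on harms is not supported as written.

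The size of any bias cannot be derived from the protocol. Under the assumed 10% rate, the chance of a spurious difference runs from about 10% to about 68% as usual-care capture falls from 75% to 25%. The trial is too small for more than large safety differences in any case, so the gain lies in a complete and even description of harms, not in a test. Which events are recorded, in whom and when is protocol content, and a later analysis plan cannot restore data that were not collected. The change is worth making, but the primary glycaemic analysis does not depend on it.

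**What to change.** - Replace the recording sentence in section 14.0 with a cause-neutral rule for both arms, from enrolment to month 12: injuries and musculoskeletal conditions, cardiovascular events, hospitalisations, deaths, and suspected diet-related events. Record relatedness as a separate field and do not use it as a condition for entry. State that reports of cardiac symptoms under section 14.0 enter this record.
- Add an adverse-event row to Table 8 at 6 and 12 months, asked with the same standard question in both communities.
- Base any between-arm description of harms on those two visits, and list events volunteered at sessions or in follow-up calls separately.

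The cost is one rewritten rule, one table row and one short question at two visits already scheduled. That means a few minutes per visit and some unrelated events recorded. A question covering the past six months relies on recall, but it does so equally in both arms.

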#### **15.0 PUBLIC HEALTH IMPACT**

- i) Only a small percentage of Malaysian adults with pre-diabetes are aware that they are at high risk of developing type 2 diabetes. Not many made any lifestyle changes as to reduce the diabetes risk.

- ii) Lifestyle modification has been shown effective in reducing the risk of diabetes in randomized control trials. However, the main challenge is to translate this evidence into a routine community setting and provide a feasible effective intervention.
- iii) There should be a concerted effort all round including smart partnership between the government agencies, Non-governmental agencies (NGOs) and research institutions to join forces to curb this problem holistically.

## 16.0 GANTT CHART

| Activities :                                           | Year 2011 |     |     |     |     |     |     |     |     |     |     |     |
|--------------------------------------------------------|-----------|-----|-----|-----|-----|-----|-----|-----|-----|-----|-----|-----|
|                                                        | Jan       | Feb | Mar | Apr | May | Jun | Jul | Aug | Sep | Oct | Nov | Dec |
| 1. Preparation of study proposal                       |           |     |     |     |     |     |     |     |     |     |     |     |
| 2. Submission to ethical review board                  |           |     |     |     |     |     |     |     |     |     |     |     |
| 3. Protocol approval from UMMC ethical board           |           |     |     |     |     |     |     |     |     |     |     |     |
| 4. Submission to IPPP for post-graduate research grant |           |     |     |     |     |     |     |     |     |     |     |     |
| 5. Preparation of study materials                      |           |     |     |     |     |     |     |     |     |     |     |     |
| 6. Health screening and recruitments                   |           |     |     |     |     |     |     |     |     |     |     |     |
| 7. Training of the trainers                            |           |     |     |     |     |     |     |     |     |     |     |     |
| 8. Randomization & Baseline data collection            |           |     |     |     |     |     |     |     |     |     |     |     |
| 9. Lifestyle interventions                             |           |     |     |     |     |     |     |     |     |     |     |     |
| Activities :                                           | Year 2012 |     |     |     |     |     |     |     |     |     |     |     |
|                                                        | Jan       | Feb | Mar | Apr | May | Jun | Jul | Aug | Sep | Oct | Nov | Dec |
| 10. Lifestyle interventions                            |           |     |     |     |     |     |     |     |     |     |     |     |
| Activities :                                           | Year 2013 |     |     |     |     |     |     |     |     |     |     |     |
|                                                        | Jan       | Feb | Mar | Apr | May | Jun | Jul | Aug | Sep | Oct | Nov | Dec |
| 11. Data collection                                    |           |     |     |     |     |     |     |     |     |     |     |     |
| 12. Data collection                                    |           |     |     |     |     |     |     |     |     |     |     |     |
| 13. Data collection                                    |           |     |     |     |     |     |     |     |     |     |     |     |
| 14. Data collection                                    |           |     |     |     |     |     |     |     |     |     |     |     |
| Activities :                                           | Year 2014 |     |     |     |     |     |     |     |     |     |     |     |
|                                                        | Jan       | Feb | Mar | Apr | May | Jun | Jul | Aug | Sep | Oct | Nov | Dec |

|                   |  |  |  |  |  |  |  |  |  |  |  |  |
|-------------------|--|--|--|--|--|--|--|--|--|--|--|--|
| 15. Data analysis |  |  |  |  |  |  |  |  |  |  |  |  |
| 16. Final report  |  |  |  |  |  |  |  |  |  |  |  |  |

